##### Differences in treatment preferences between patients and clinicians

We will test the difference of the means of *b *between the patients (*b*_*p*_) and clinicians (*b*_*c*_) using an unpaired *t *test. The observed distribution of *b*_*p *_in our preliminary work was highly skewed. This was because patients clustered at the highest *b *offered. For this study, we propose to offer a maximum *b *that is twice as large as the maximum *b *offered in our preliminary study. Furthermore, we will be studying a relatively large number of patients and clinicians with distribution of the means approximating the normal distribution with SEM = SD/vn. Our sample sizes will be considerably larger than 30, a size which is often taken as a guideline threshold, above which the sample distribution of the sample mean will be reasonably normally distributed, even if the distribution of individual values is substantially skewed. Thus, the use of the t-test is appropriate. However, we will also use the Mann-Whitney test, a non-parametric test that does not require the assumption of normality of the distribution. After identifying pertinent subgroups in the analysis to Research Question 1, we will conduct modified *t *tests to test the difference of the means of *b *between the patients and the subgroup of clinicians of interest. A modified *t *test is based on the pooled estimate of variance from all the subgroups [33]. The resulting *P *values can be adjusted for multiple comparisons using the Bonferroni method (multiplying the resulting *P *value by the number of paired comparisons performed).

We will also determine the proportion of patients and clinicians who would choose to take or recommend warfarin when b = 0.5 (that is, when patients experience one bleed for every two strokes prevented). We designate this value of b as *b*_*RCT *_because it is the average number of additional bleeds per stroke prevented reported in randomized trials of warfarin vs. aspirin from the meta-analysis [11] (Table 1). We will test the difference in these proportions using Fisher's exact test and will estimate the exact 95% confidence interval of the odds ratio for the proportions of patients and clinicians who would use warfarin at *b*_*RCT*_. We will also determine the proportion of clinicians from pertinent subgroups (identified in Research Question 1) who would choose to recommend warfarin at *b*_*RCT *_= 0.5. Then, we will test the differences between this proportion and the proportion of clinicians not in the subgroup recommending warfarin when *b *= 0.5, as well as the difference between the proportion recommending in the subgroup and the proportion of patients who would choose to take warfarin at *b*_*RCT*_.

#### Research question 3

What explains any differences in treatment preferences between patients and clinicians?

##### Differences in utilities between patients and clinicians

In responding to the feeling thermometer, each participant will provide 5 utilities (for major and minor stroke, major bleed, using daily aspirin, using daily warfarin). We will compare the distributions of each of these utilities in patients and clinicians using the Mann-Whitney test, a nonparametric test, as these variables are usually highly skewed. We will also use the *t *test to test the difference of the means of the utilities between patients and clinicians. To evaluate the consistency between participant utilities for health states and *b *(that is, the number of additional bleeds per stroke prevented at the point of switch from warfarin to aspirin in the probability trade-off exercise) we will examine scatter plots of each of the utilities and *b*. Also, we will estimate the correlations between each of the utilities for the 5 health states and *b*. We will conduct linear regression analysis with *b *as dependent variable and with utilities as independent variables. We will attend to the interaction between the utilities, which we anticipate being a key issue, in this analysis.

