▪ Direct contrast of the average utilities for stroke, bleeding, and using antithrombotic agents between patients and clinicians.

To promote and focus debate the facilitator may ask the following questions to the group (if appropriate given the results):

▪ Can you describe, in your own words, the thought processes you went through in making your decisions during the probability trade-off and feeling thermomether exercises?

▪ Do you think that your answers to probability trade-off and feeling thermomether are consistent with each other? Why or why not?

▪ Which one of the exercises (probability trade-off, feeling thermomether) do you think captured more accurately the true relative values you place on avoiding bleeds and preventing strokes? Why?

Depending on the results during phase 1 (individual interviews), other questions could be relevant, including the following:

▪ You placed a relatively higher value on bleeding and a relatively lower value on stroke when making a decision (probability trade-off) than when we looked at those outcomes separately (feeling thermomether). Why?

▪ Can you think of plausible explanations for the differences between clinicians and patients choices and preferences for treatment?

▪ Can you think of plausible explanations for the differences between the answers that clinicians gave when they participated as patients and when they participated as clinicians?

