##### Analysis of focus group data

Data from the 6 focus groups sessions will be transcribed verbatim and checked for accuracy by comparing the written text to each audio tape. Initially, two experienced researchers in qualitative methods using an editing approach [34] will work independently to develop a coding system to identify the major themes from data contained in two of the focus groups transcripts. The researchers will then meet to compare the consistency and meaning of the codes developed and their application in the first set of two transcripts. Based on these results, researchers will then modify the coding scheme based and establish an audit trail [35]. Then, the two researchers, working independently, will code two further focus group transcripts using the coding scheme and again compare results, discussing and resolving any disagreements. This iterative process will continue until researchers finish coding all the transcripts. The codes (themes) developed will focus on capturing the kinds of thought processes and rationales that clinicians used to make their treatment preferences in the first phase interviews. In the focus group, clinicians will receive feedback on the results of the first phase interviews to set the context for the discussion of reasons for these preferences. The results will include the distribution of preferences of patients and clinicians, differences in these distributions, and the degree of internal consistency between clinicians' treatment preferences and their utilities for the relevant health states.

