Our review of the evidence suggests that it is more likely that we will confirm substantially different treatment choices in clinicians and patients. This result would suggest that current low rates of anticoagulation in atrial fibrillation reflect clinician and not patient values, and mandate urgent development and testing of interventions to increase rates of anticoagulation, and thus prevent unnecessary strokes. Such findings would not, however, explain why clinician and patient choices differ. We see two leading possibilities. One is that, relative to patients, clinicians experience the post-stroke state as relatively less aversive, and having a gastrointestinal bleed as relatively more aversive, than do patients. The second explanation is that clinicians and patients share the same values for stroke and bleeding, but the circumstances of clinical decision-making lead clinicians to make different choices. In particular, we hypothesize that omission bias associated with efforts to reduce clinician-generated risk, may explain the results. This explanation posits that clinicians put more weight on commission of a behavior that leads to adverse consequences (bleeding through warfarin administration) than an omission of behavior that could lead to beneficial consequences (stroke prevention through warfarin administration). We will explore this issue through direct measurement of utilities for stroke and bleeding, and through focus groups with the participating clinicians.

On completion of this study, we will hope to achieve major advances in understanding clinician and patient decision-making in atrial fibrillation. Our anticipated results will challenge investigators, medical educators, and health care providers to develop and test strategies to deal with differences in clinician and patient choices. Our results will guide the development of these strategies, which may include innovations in undergraduate and post-graduate education, enhancements to the clinical encounter to facilitate patient-clinician communication and shared decision-making, increasing use of decision support tools in clinical practice, and monitoring and feedback of clinician success in providing optimal anticoagulation in patients with atrial fibrillation. For example, our experience using decision boards in this study will inform the organization and conduct of a randomized controlled trial to test their efficacy in helping patients with atrial fibrillation make informed choices.

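### The Research Question 3 consistency analysis measures association between utilities and b, so it cannot show or size a shift in the level of b relative to utilities

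*Protocol article*

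**What the plan says.** The protocol article, under Differences in utilities between patients and clinicians, states a purpose: "To evaluate the consistency between participant utilities for health states and" *b*, the number of additional bleeds accepted per stroke prevented. Three tools follow. They are scatter plots, a correlation of each of the five utilities with *b* ("we will estimate the correlations between each of the utilities for the 5 health states and" *b*), and a linear regression with *b* "as dependent variable and with utilities as independent variables", with attention to interactions among the utilities. No term for patient versus clinician or for the assigned role is named there, and no value of *b* implied by the utilities is calculated.

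Three other places show what this analysis should inform:

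- The Focus group agenda has a prompt, for use if the results call for it: "You placed a relatively higher value on bleeding and a relatively lower value on stroke when making a decision" than when rating the outcomes separately.
- Analysis of focus group data promises clinicians feedback on "the degree of internal consistency between clinicians' treatment preferences and their utilities for the relevant health states".
- The Discussion names two leading explanations for a clinician–patient difference: different values, or the same values with different choices. Under the second it singles out omission bias, in which "clinicians put more weight on commission of a behavior that leads to adverse consequences" than on an omission.

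The same section also plans, for each utility, a Mann-Whitney test and a *t* "test to test the difference of the means of the utilities between patients and clinicians". Under Research Question 2 the article says "We will test the difference of the means of" *b* between patients and clinicians. Clinicians are randomised to answer as a patient or as a recommending clinician, and role is among the characteristics in the exploratory regression of *b* under Research Question 1.

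**The concern.** The focus-group prompt and the omission-bias hypothesis both describe a difference in level: *b* sits lower than the person's own ratings would suggest. A correlation asks something else, namely whether people who rate a bleed as worse also tolerate fewer bleeds. All clinicians could discount their own values by the same amount and still be ranked perfectly by those values. A strong correlation would then be read as consistency while the shift was present. A regression fitted freely, with no group or role term, has nothing in it that estimates the shift.

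At stake is the separation of the article's two explanations, which is the purpose of Research Question 3.

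**Working it through.** **Inputs from the article.** There are 96 patients and 96 clinicians, with α = 0.05 (two-sided reproduces Table 2). Mean *b* in the previous study was 2.2 (SD 0.9) in patients and 1.3 (SD 0.8) in clinicians. The difference is 0.9 and the ratio 1.3/2.2 = 0.59.

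**Assumed inputs.** The article gives no utility distributions. The main simulation (2,000 studies) used the same ratings in both groups: means 20 (major stroke), 60 (minor stroke), 70 (bleed), 90 and 95 (the two treatment states), with SDs 12, 12, 12, 6 and 4. *b* was 2.2 plus slopes of −0.02, −0.02, 0.03, 0.01 and 0 on the centred ratings, plus normal noise of SD 0.65. The SD of *b* was then about 0.81.

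**The plan's own figure.** For 96 v 96 at 0.4 SD: 0.4/√(2/96) = 2.77; 2.77 − 1.96 = 0.81; Φ(0.81) = 0.79. This matches Table 2, and all 16 cells reproduce.

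**Algebra.** For any constant c and any k > 0, corr(u, k·b + c) = corr(u, b). In the regression b = a + u′β + e, subtracting δ from every *b* changes only a, to a − δ. Multiplying every *b* by k turns a and β into k·a and k·β. So an additive shift sits wholly in the intercept. A proportional shift does move the slopes, but the plan gives no reference value against which to judge them.

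**Simulation, shift in all clinicians:**

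| Clinicians' *b* | Largest change in the 5 within-clinician correlations | Largest change in slopes | Change in intercept | Pooled correlation with bleed utility | Power, *t* test on *b* | Power, group term given utilities |
|---|---|---|---|---|---|---|
| unchanged | 0.000 | 0.000 | 0 | 0.44 | 0.06 | 0.05 |
| −0.9 | 0.000 | 0.000 | −0.9 | 0.38 | 1.00 | 1.00 |
| −0.4 | 0.000 | 0.000 | −0.4 | 0.43 | 0.92 | 0.98 |
| × 0.59 | 0.000 | 0.013 | −0.33 | 0.35 | 1.00 | 1.00 |

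The pooled correlation falls a little, but not in a way that a reader would recognise as a shift.

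**Halving *b*.** In a second model, *b* follows the utility-implied threshold b* = (0.5·D_major + 0.5·D_minor)/D_bleed, where D = 100 − rating. With mean disutilities of 80, 40 and 35, b* at the means is (40 + 20)/35 = 1.71. With lognormal noise of SD 0.5, the correlation of *b* with the bleed utility was 0.58 when *b* was fully consistent and 0.58 when every clinician's *b* was halved, significant in 100% of studies both times. With noise SD 1.0 it was 0.35 (95% significant) against 0.34 (93%). Repeats with other assumed inputs gave 0.57 against 0.56, and about 0.54 to 0.55.

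**Shift in the recommending role only (48 v 48 assumed).** The role contrast has power 1.00 for a shift of 0.9 and 0.64 for 0.4. In SD units, 48 v 48 gives power 0.49 at 0.4 SD and reaches 80% at about 0.58 SD. If the shift is the same in both roles, the role contrast rejects only at about its 5% level.

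**Reading the separate tests together.** With no true difference in utilities, at least one of five unadjusted utility tests falls below 0.05 in about 22% of studies (1 − 0.95⁵ = 0.226). In a mixed case, clinicians rated bleeding slightly worse (disutility 40 v 35) and also lowered *b* by 30%. The pattern of different *b* with no stroke or bleed utility differing then appeared in 32% of studies. In 66%, *b* and at least one utility both differed, which points to different values and hides the shift. A separate mixed-case run gave that first pattern in 10% to 18%.

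**The case against.** A reader might infer that the study cannot detect omission bias at all. The documents do not support that. The Discussion says the question will be explored by measuring utilities and through focus groups. Similar utilities with different *b* is the pattern the second explanation predicts, and both halves are tested. In the halving model the planned Mann-Whitney test on *b* detects the change in 100% (noise SD 0.5) or 99% (SD 1.0) of studies, and the *t* test in 99.9% or 87%. For a 25% reduction the Mann-Whitney figures fall to 84% and 39%. The randomised role also bears on the question, and the facilitator will contrast the average results of the two exercises. All of this stands.

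Three further readings go too far:

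- The regression is not unaffected by every shift: in one run, halving *b* took the bleed slope from 0.094 to 0.046.
- The feedback to focus groups need not be wrong, because the article does not say that the degree of internal consistency will be the correlation.
- Omission bias is a hypothesis under the second of two leading explanations, not the only one.

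It can also be said that a condensed article may leave a group term to a fuller plan. But the article does name the tools for the stated purpose, and those tools measure something else.

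The indirect route remains limited. It takes equal values from non-significant tests, it never estimates the difference in *b* left after utilities, and it separates the explanations poorly when both act. The role contrast is exploratory and misses a bias common to both roles. Focus groups give reasons, not an estimate.

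**Conclusion.** The concern holds for the consistency analysis under Research Question 3, not for the study as a whole. Correlations and a regression without a group or role term cannot show or quantify a shift in the level of *b* relative to utilities. For the correlations within a group this is exact algebra and needs no assumption. An additive shift also leaves the slopes unchanged.

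The size of the gap elsewhere rests on assumed utilities. The indirect pattern appeared in 10% to 32% of mixed-case studies. A contrast of *b* given the utilities kept its size near 5% and detected halving in 89% to 100%.

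Testing the mean of log(b/b*) against zero would not be a sound replacement. It needs ratio-scaled ratings, and it needs a lifelong stroke outcome and a single bleed to be comparable in duration. log(b) is also undefined at *b* = 0, which was up to 6% of halved values.

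**What to change.** - Keep the scatter plots and correlations as descriptive, and state that they will not be read as evidence of consistency.
- Base the Research Question 3 statement on two contrasts in *b* given the utilities, each with a 95% CI: clinician versus patient, and recommending role versus patient role among clinicians. Group and role terms in the planned regression of *b* on utilities would do this.
- Report the role difference in *b* without utilities as well. The ratings are themselves given under the assigned role, so the adjusted contrast is no longer a purely randomised comparison.
- As a sensitivity analysis, compare observed *b* with b* between groups and between roles. State beforehand how *b* = 0 and a bleed rated 100 are handled. Do not test the mean of log(b/b*) against zero as an absolute standard.

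The cost is wording and a little more analysis, since every input is already collected. The group contrast assumes that clinicians and patients use the thermometer in a similar way, and error in the ratings would leave part of a true difference in values in the group term. Both limits should be stated with the result.

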##### Analysis of focus group data

Data from the 6 focus groups sessions will be transcribed verbatim and checked for accuracy by comparing the written text to each audio tape. Initially, two experienced researchers in qualitative methods using an editing approach [34] will work independently to develop a coding system to identify the major themes from data contained in two of the focus groups transcripts. The researchers will then meet to compare the consistency and meaning of the codes developed and their application in the first set of two transcripts. Based on these results, researchers will then modify the coding scheme based and establish an audit trail [35]. Then, the two researchers, working independently, will code two further focus group transcripts using the coding scheme and again compare results, discussing and resolving any disagreements. This iterative process will continue until researchers finish coding all the transcripts. The codes (themes) developed will focus on capturing the kinds of thought processes and rationales that clinicians used to make their treatment preferences in the first phase interviews. In the focus group, clinicians will receive feedback on the results of the first phase interviews to set the context for the discussion of reasons for these preferences. The results will include the distribution of preferences of patients and clinicians, differences in these distributions, and the degree of internal consistency between clinicians' treatment preferences and their utilities for the relevant health states.

Data from focus groups transcripts will be entered into Atlas.ti , a computer friedly software program that assists with data management, search, and retrieval of textual information [35]. Data analysis will occur at three different levels: description, analysis, and interpretation [36]. In terms of description, we will develop a structured form to summarize key information from each focus group transcript. We will also describe data segments from the transcripts and code them by theme. Next, we will undertake a comparative a nalysis of themes across the six focus groups as a whole to identify similarities and differences in the data. Finally, we will identify how participants think about the underlying thought processes they used to determine their preferences and point out implications for practice. During the data analysis and write up stages, we will ask clinicians from each focus group to review and provide feedback on the written summary prepared for their specific group in order to ensure that these summaries accurately reflect the key themes from the participants' perspective [32,37,38].

##### Sample size estimation

We require six focus groups, 1 of generalists and 2 of cardiologists at Barcelona, 1 of generalist at Galicia and País Vasco. We will undertake 1 group of patiens in each site. Ideally, each group should have 8 to 10 participants. We anticipate that not every clinician will be able to participate. To ensure 8 clinicians per group, we will enroll 12 potential participants per group. We will construct the focus groups to maximize homogeneity of specialty, experience with patients with atrial fibrillation, and treatment preferences during individual interviews (phase 1). From our survey of faculty at the 3 sites, less than 10% of clinicians at each site are not eligible. Therefore we would need to enroll 20% of eligible clinicians at each site to achieve our sample size of 96 clinicians which will ensure adequate numbers for the focus groups.

Our study should be powered to determine differences in means of *b*_*p *_and *b*_*c*_, that is, differences in the treatment preferences of patients and clinicians, the key variable. In our previous study, the effect size (difference in mean *b *between patients and clinicians) was 0.9 (this is calculated from sample means (and SDs) of 2.2 (0.9) and 1.3 (0.8) in the patients and clinicians, respectively). Although it is not immediately evident what magnitude of the difference in *b *would be clinically important, readers and commentators have uniformly considered the differences we showed as important. Table 2 shows the power we would have with the proposed sample size of 96 clinicians and an equal number of patients, and also illustrates the limited impact of increasing the number of patients from 1:1 to 1:3. Therefore, given the number of clinicians available to us, we will have ≥ 80% power to detect differences in means ≥ 0.4·SD. We will have ≥ 80% power to detect differences in means of *b*_*p *_and *b*_*c *_≥ 0.75·SD between subgroups of ≥ 20 clinicians and 96 patients. In summary, after enrolling 96 patients and 96 clinicians we will have ≥ 80% power to detect (1) *b*_*p *_- *b*_*c *_> 0.4 SD, (2) odds ratio ≥ 2.6 of the proportion of patients and clinicians with *b *> *b*_*RCT *_(if that proportion is 0.63 or smaller among clinicians), and (3) a difference in mean utilities of ≥ 0.4 SD. We need to enroll 96 clinicians to ensure 8 members per focus group. Enrolling more than 96 patients has a very small impact on power. Thus, we will recruit 96 patients and 96 clinicians for this study.

**Table 2 T2:** Power to detect differences in means of *b*_*p *_and *b*_*c *_0.2 to 0.5 standard deviation units (α = 0.05)

** *Sample* **		*b*_*p *_- *b*_*c *_difference in SD units			
Clinicians	Patients	0.2	0.3	0.4	0.5
96	96	.28	.54	.79	.93
96	144	.33	.62	.86	.97
96	192	.36	.67	.89	.98
96	288	.39	,71	.92	.99

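### The 80% power claim for an odds ratio of 2.6 has no lower bound and fails below a clinician proportion of about 0.20, and the cited prior data point above its upper limit

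*Protocol article*

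**What the plan says.** All the power statements are in the protocol article under Sample size estimation. The sample is fixed there: "Thus, we will recruit 96 patients and 96 clinicians for this study". Three claims of at least 80% power follow.

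- **Means.** The text states that "we will have ≥ 80% power to detect differences in means ≥ 0.4·SD", and its closing summary repeats 0.4 SD for b and for the utilities. The matching row of Table 2 reads "96 96 .28 .54 .79 .93" for differences of 0.2, 0.3, 0.4 and 0.5 SD.
- **Subgroups.** A difference of 0.75 SD between at least 20 clinicians and the 96 patients.
- **Proportions.** An odds ratio of at least 2.6 for the proportions of patients and clinicians with b above b_RCT, "if that proportion is 0.63 or smaller among clinicians".

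The same section gives the prior study's b as 2.2 (SD 0.9) in patients and 1.3 (SD 0.8) in clinicians. Under Research question 2, b_RCT is set at 0.5, and the test for the proportions is named: "We will test the difference in these proportions using Fisher's exact test". For subgroup t tests, that section offers a Bonferroni correction as something that can be done and fixes no number of comparisons.

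**The concern.** For a fixed odds ratio and sample size, power for two proportions falls off towards both 0 and 1. A condition with only an upper limit therefore cannot be right for every smaller proportion. The upper limit also has to be compared with what is known about clinicians. The article prints the prior mean and SD in the same paragraph as the 0.63 limit but does not relate one to the other, and it gives no power above 0.63.

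The comparison at b_RCT matters because it represents the trade-off reported in the trials of warfarin against aspirin. The Discussion says that similar choices by patients and clinicians would lead to the conclusion that current anticoagulation rates are appropriate. A non-significant odds ratio would thus be interpreted, and the reader would judge it by the stated power.

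**Working it through.** **Inputs.** 96 per group, α = 0.05, Fisher's exact test for proportions, t test for means, b_RCT = 0.5, prior b of 1.3 (0.8) and 2.2 (0.9). The article does not say whether tests are two-sided. Two-sided testing reproduces Table 2, whereas one-sided testing would give 0.868 at 0.4 SD, so two-sided is assumed.

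**1. Reproducing the figures for means.** The noncentrality is d·√(n₁n₂/(n₁+n₂)), which at d = 0.4 is 0.4·√48 = 2.77 with 190 degrees of freedom. Power at 0.2, 0.3, 0.4 and 0.5 SD is 0.281, 0.543, 0.787 and 0.931, in agreement with Table 2. Power of 80% is reached at 0.406 SD.

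**2. Reproducing the 0.63 limit.** The patient proportion is p_p = OR·o/(1 + OR·o), where o is the clinician odds. With o = 0.63/0.37 = 1.703, p_p = 4.427/5.427 = 0.816. For a Wald test of the log odds ratio:

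- SE = √[1/(96·0.63·0.37) + 1/(96·0.816·0.184)] = 0.338
- power = Φ(ln 2.6/0.338 − 1.96) = Φ(0.87) = 0.808

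At 0.64 this method gives 0.7996, so it returns the stated 0.63 limit.

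**3. The planned test.** Fisher power comes from summing the binomial probabilities of all 97 × 97 outcomes with p ≤ 0.05, at an odds ratio of 2.6:

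| Clinician proportion | Patient proportion | Fisher power | Log odds ratio method |
|---|---|---|---|
| 0.05 | 0.120 | 0.325 | 0.396 |
| 0.10 | 0.224 | 0.590 | 0.626 |
| 0.15 | 0.315 | 0.733 | 0.755 |
| 0.20 | 0.394 | 0.807 | 0.826 |
| 0.40 | 0.634 | 0.882 | 0.895 |
| 0.60 | 0.796 | 0.812 | 0.830 |
| 0.63 | 0.816 | 0.788 | 0.808 |
| 0.70 | 0.859 | 0.715 | 0.738 |
| 0.80 | 0.912 | 0.538 | 0.580 |
| 0.84 | 0.932 | 0.435 | 0.494 |
| 0.85 | 0.936 | 0.407 | 0.471 |

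Under Fisher's test the claim holds from about 0.20 to about 0.61. The failure at low proportions does not depend on the choice of test, since the method that returns the 0.63 limit also falls below 80% at 0.15. The odds ratio detectable with 80% Fisher power is 2.64 at 0.63, about 4.0 at 0.80 and about 5.2 at 0.84.

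**4. What the prior data suggest.** Assume b is normal.

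- Clinicians: (0.5 − 1.3)/0.8 = −1.00, so P(b > 0.5) = 0.841. A gamma distribution with the same mean and SD gives 0.87, and a lognormal gives 0.92.
- Patients: (0.5 − 2.2)/0.9 = −1.89, so P(b > 0.5) = 0.971.
- Implied odds ratio: (0.9705/0.0295)/(0.8413/0.1587) ≈ 6.2, for which Fisher power is 0.853.

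**5. Subgroups.** For 20 against 96 at 0.75 SD the noncentrality is 0.75·√(20·96/116) = 3.05 with 114 degrees of freedom. Power is 0.857 unadjusted, 0.781 with Bonferroni for two comparisons and 0.732 for three.

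**The case against.** A reader might infer that all of the article's power statements are miscalculated. They are not. Table 2 reproduces, the subgroup figure is correct at α = 0.05, and the odds ratio claim at 0.63 gives 0.81 by the log odds ratio formula. Planning a Fisher test with such a formula is common, and the loss at exactly 0.63 is about one point. The gap at 0.4 SD is also about one point, and Table 2 shows it openly. Bonferroni is optional, the subgroups are to be chosen after an exploratory regression, and no number of comparisons is fixed, so the adjusted subgroup figures are conditional illustrations.

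A reader might also infer that the comparison of proportions has only about half its stated power. The documents do not support that:

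- The 0.63 limit is disclosed, so a proportion above it lies outside the claim.
- The article reports no prior proportion. The 0.84 is an approximation from a mean and SD, taken from a study of warfarin against no treatment with 8 strokes avoided, not 3 as here. Its scenarios also left out the inconvenience of warfarin and deaths, which are now presented.
- Taking 0.84 from the prior data while keeping 2.6 uses only half of those data. Taken whole, they imply an odds ratio of about 6.2 and power of about 85%.

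These objections stand. It is also fair to say that proportions below 0.20 look unlikely if the prior data are any guide. None of this rescues the unbounded condition, which is false as written. Nor does it supply the missing power for 2.6 at high proportions, where the only data cited would place clinicians.

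**Conclusion.** The point holds for the odds ratio claim. At least 80% power for 2.6 is available only for clinician proportions of about 0.20 to 0.61 under Fisher's test. Power is 0.73 at 0.15 and 0.59 at 0.10, and this part needs no assumption beyond two-sided testing at 0.05.

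Above the limit, the fault is a condition that was not compared with the available data; the arithmetic is not at fault. Near 0.84, power for 2.6 is about 44% and 80% needs about 5.2. That rests on assumed normality and on carrying over a different treatment comparison.

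The 0.4 SD wording (0.787 against a stated 80%) is a small inconsistency between text and table. The subgroup statement is correct unadjusted but would not survive even two Bonferroni-adjusted comparisons. The main comparison of mean b is not threatened: the prior difference of 0.9, over a root-mean-square SD of √((0.81 + 0.64)/2) = 0.85, is about 1.06 SD.

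**What to change.** Under Sample size estimation:

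- Restrict the claim for an odds ratio of 2.6 to clinician proportions of about 0.20 to 0.61 under Fisher's exact test.
- Add the power for 2.6, or the odds ratio detectable with 80% power, at 0.80 to 0.85. Power is 54% at 0.80 and 41% at 0.85; the detectable odds ratio is about 4.0 at 0.80 and about 5.2 at 0.84.
- Write 79% power at 0.4 SD, or 80% at 0.41 SD, for both b and the utilities.
- Label the subgroup power as unadjusted, and note that it falls below 80% if Bonferroni is applied to two or more comparisons.

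The cost is text only. Enrolment, tests and analyses stay as planned; some stated figures become less favourable.
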